## Introduction

While active-direct euthanasia (killing on demand) is prohibited in Switzerland under Art. 114 of the Swiss Penal Code (StGB), physician-assisted dying (PAD) is not regulated by the law (Art. 114 section 1 StGB). Art. 115 of the StGB prohibits assisted dying only if it is performed for “selfish motives” (Art. 115 section 1 StGB). In our study, we use the term PAD for the concept of physician-assisted suicide as it is performed in Switzerland.

The Swiss Academy of Medical Sciences (SAMS) does not consider PAD as a medical activity but respects it as a “legally permissible activity” that a physician may perform as a “personally responsible decision” after careful examination of the necessary prerequisites. The SAMS (1) lists the following necessary criteria for the granting of PAD: a patient must have preserved decision-making capacity (DMC) regarding the wish to die. “It must be documented that incapacity has been carefully excluded by the physician.” The wish to die must be self-determined, deliberate, and permanent. If a patient is dependent on people in his environment, their possible influence on the wish to die must be carefully considered. Furthermore, the comprehensibility or justifiability of the wish to die in the patient's concrete individual life situation must be examined. Medically indicated treatment options, as well as alternative support options, must have been sought and exhausted or must have been declared unacceptable by the patient who was capable of decision-making in this regard. In addition, a patient's suffering must be classified as “intolerable” according to the current version of the SAMS ethical guidelines (2). The term intolerable suffering replaced the term terminal illness, which was valid as a prerequisite for PAD until 2018 (3). However, intolerable suffering is still not a sufficient criterion for PAD; preserved DMC and exhausted or unacceptable alternative options are additional necessary prerequisites (4).

A patient's wish for PAD can lead to the professionals perceiving a moral conflict between the ethical principle of respect for patient autonomy, and the ethical principle of beneficence in the sense of preserving the patient's life (ethical principles according to Beauchamp and Childress) (5).

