In the last years, PAD practices have expanded internationally. While in Switzerland and the Benelux countries PAD practices have been legal for a long time, other European countries such as Germany and Austria have recently changed their jurisdiction while the terms and conditions of implementation are not available yet (8, 9). Outside of Europe, PAD is legal in Colombia, Canada, three states in Australia, and 11 states in the USA. Nevertheless, assisted dying is subject to controversial medical ethics and public debate internationally, and also in Switzerland. For example, the law does not specify who may get access to PAD, and professional societies disagreed on this subject for 3 years: while intolerable suffering was accepted as a key criterion by the SAMS, the Swiss Medical Association (FMH) rejected this because it deemed the term “intolerable suffering” as imprecisely defined, insufficiently delimitable, and too strongly dependent on the subjective assessment of the patient. Therefore, the decision on granting assisted dying may hold great uncertainty for the physicians in charge. Consequently, the FMH postulated the following: “Physician-assisted dying should therefore be limited to those patients who are suffering from a fatal illness and whose condition will not improve with proper medical treatment. Such a diagnosis can be made by a physician with sufficient reliability” (10). This requirement particularly discriminated against mentally ill patients with a prolonged wish to die, since although they can suffer intolerably in the same way as somatically ill patients, their illness is not typically classified as terminal (10, 11). In May 2022, as a result of the cooperation of the SAMS and the FMH, both institutes accepted an updated version of the guidelines. As in the former version of 2018 they require that the intolerable suffering is caused by symptoms of a disease and as a new complement the severity of the condition must be substantiated by an appropriate diagnosis and prognosis (2).

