### Primary objective

The current study investigates the acceptance of PAD in the general population on the one hand, and in the medical profession, on the other hand, depending on (1) the type of illness (somatic/mental), (2) the presence of intolerable suffering, (3) DMC, (4) the availability of therapeutic options, and (5) the terminal nature of the illness based on case vignettes. Furthermore, it examines to what extent the stigmatization of mentally ill persons is linked to the acceptance of their wish to die. It is an exploratory analysis to provide first insights into the current situation in Switzerland, paving the way for further research projects to form hypotheses. Within the scope of this project, the following research questions will be investigated:

Are there associations between the type of illness (somatic vs. mental) and the decision on whether a person should be granted access to PAD?Does the reasoning behind accepting the legitimacy of wishes to die correspond to the conflict between professional societies (terminal illness vs. intolerable suffering)?To what extent does the acceptance of PAD in concrete situations described in case vignettes correspond to the positioning on the SAMS criteria of 2004, 2018, and 2021?Which criteria do participants from the public and the medical profession indicate as relevant to them in an open answer format?Is there an association between the level of stigmatization and the assessment of whether a person should be granted access to PAD?Are there differences between medical professionals and the public regarding research questions 1–5?

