#### Case vignettes and assessment of PAD

It is essential that the persons taking part in the study fully understand what is meant by PAD and this cannot be taken for granted when addressing the general population. Physician-assisted dying is therefore explained in lay terms before the questions concerning PAD are posed.

For the vignettes, three cases were created: one about a person suffering from a non-terminal somatic illness, one about a person suffering from a terminal somatic illness, and one about a person suffering from a non-terminal mental illness. For each of these cases, there will be 16 different versions. Common to all of them will be the three factors of well-consideration, self-determination, and permanence of the desire to die. In contrast, the factors tolerability vs. intolerability of suffering, DMC vs. incapacity, the absence vs. presence of a therapeutic option, and the gender of the person depicted differ and are permuted with each other in the vignettes. This will result in a total of 48 different case vignettes. Expert ratings will be used to assess the interrater reliability of the case vignettes. To ensure that the assessment of different raters has a concurrent outcome, interrater reliability is calculated using Fleiss' kappa with a target value of at least 0.8, indicating substantial agreement (22). This measure has the advantage over other kappas such as Cohen's kappa that interrater reliability by more than two raters can be tested.

Each participant will be randomly assigned three case vignettes—one (out of 16 possible variations) about a person suffering from a non-terminal somatic illness, one (out of 16 possible variations) about a person suffering from a terminal somatic illness, and one (out of 16 possible variations) about a person suffering from a non-terminal mental illness. For these three concrete situations, the participant will be asked to assess whether physician-assisted suicide should be granted or not. The participant will define the degree of his or her approval or disapproval on a 5-point Likert scale and will be asked to justify the decision by describing his or her motives in an open answer format. Furthermore, participants will be asked to select those items from a list of alternative justifications that are decisive for their judgment.

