### Statistical analysis

The primary endpoint will be the degree of consent to PAD depending on the type of illness (somatic vs. mental).

In addition, the following secondary endpoints have been defined:

1. Degree of consent to PAD as a function ofa. the intolerable sufferingb. DMCc. the availability of therapeutic optionsd. the terminal nature of the illness.2. Positioning of the respondents to the SAMS criteria of 2004, 2018, and 2021.a. Spontaneously expressed opinions in an open answer format in the context of a qualitative evaluation.b. Agreement or disagreement when presented SAMS criteria of 2004, 2018, and 2021.3. Association between the positioning of the respondents on the SAMS criteria of 2004, 2018, and 2021, and the evaluation of the case vignettes.4. Association between the degree of stigmatization and the assessment of PAD.5. Comparison of the primary and secondary endpoints between the two groups.

The statistical analysis of the collected data will be done with a standard statistical package, either IBM SPSS Statistics (IBM Corp, released 2020, IBM SPSS Statistics for Windows, Version 27.0, Armonk, NY: IBM Corp.) or R Studio (RStudio Team, released 2020, RStudio: Integrated Development for R. Boston, MA: RStudio, PBC). The descriptive statistics of the sample characteristics will be performed separately for the two groups and the whole sample. For binary and categorical variables, we will report frequencies in numbers and percentages; for continuous variables, we will report the mean and standard deviation, and the median and interquartile range, respectively. Given the fact that our research project is an exploratory study, we do not explicitly specify significance levels. The primary endpoint [level of PAD consent as a function of the type of illness (somatic vs. mental)] will be evaluated in a simple regression analysis with the level of PAD consent as the dependent variable and type of illness as the independent variable. In a multiple regression analysis, we will further examine the association of demographic factors such as gender with the dependent variable. The variables general population/medical professional and gender will be controlled for statistically whenever necessary. The secondary endpoints will be evaluated—as far as possible—with the same analyses. To explore the responses from the free-text fields, computer-assisted content analysis will be used (MAXQDA12; VERBI Software GmbH, Berlin, Germany).

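### Secondary endpoint 3 relates guideline agreement to consent without using whether the rated vignette meets the guideline, so its slope does not measure the correspondence asked about in research question 3

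*Protocol article*

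**What the plan says.** The Primary objective section asks: "To what extent does the acceptance of PAD in concrete situations described in case vignettes correspond to the positioning on the SAMS criteria", for the successive guideline versions. The Statistical analysis section turns this into secondary endpoint 3: "Association between the positioning of the respondents on the SAMS criteria of 2004, 2018, and 2021, and the evaluation of the case vignettes".

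The method is given once for all secondary endpoints: "The secondary endpoints will be evaluated—as far as possible—with the same analyses". The model being reused is that of the primary endpoint, which "will be evaluated in a simple regression analysis with the level of PAD consent as the dependent variable and type of illness as the independent" one. It is followed by: "In a multiple regression analysis, we will further examine the association of demographic factors such as gender with the dependent variable". Group (population or physician) and gender are controlled for where needed.

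The Introduction describes criteria that must hold together. Intolerable suffering took the place of terminal illness in 2018, but is not sufficient, since "preserved DMC and exhausted or unacceptable alternative options are additional necessary prerequisites". On the newest version it says that "as a new complement the severity of the condition must be substantiated by an appropriate diagnosis and prognosis".

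The section on case vignettes lists what differs between the 16 versions of each case: "the factors tolerability vs. intolerability of suffering, DMC vs. incapacity, the absence vs. presence of a therapeutic option, and the gender of the person depicted". Type of illness and terminal nature differ between the three cases. Each respondent rates one randomly chosen version of each case on a five-point consent scale. Agreement with the guidelines is also scored from 1 (full rejection) to 5 (full agreement). No section classifies a vignette as meeting or failing a guideline version.

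**The concern.** Correspondence is conditional on the case being judged. Someone who endorses a guideline and applies it should accept the vignettes that satisfy it and refuse those that do not. Because the components are permuted, most vignettes fail at least one necessary condition, so a faithful endorser will refuse most of them. A regression of consent on agreement, taken over all vignettes, sees only the endorser's low average consent.

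People who reject a guideline may do so because it is too strict or because it is too permissive. The first group consents more than the endorsers and the second less, so they pull the overall slope in opposite directions. The estimate then reflects the mix of reasons for rejection rather than whether stated position and concrete judgement agree. For a study meant to generate hypotheses, a sign that cannot be interpreted is a poor starting point.

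**Working it through.** 1. **Vignette count.** Three cases, each with four two-level factors: 3 × 2⁴ = 48. This reproduces the article's figure.

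2. **Vignettes that meet the criteria.** The coding is an assumption taken from the Introduction, because the guideline texts are not reproduced. Strict coding requires that no therapeutic option is present. Loose coding disregards that factor, since an available option may be unacceptable to the patient.

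| Version | Strict | Loose |
|---|---|---|
| 2018: intolerable suffering, DMC, no option | 2 of 16 per case; 6/48 = 1/8 | 12/48 = 1/4 |
| 2004 (inferred): terminal, DMC, no option | 4 of 16 terminal versions; 4/48 = 1/12 | 8/48 = 1/6 |

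3. **Overall slope when everyone is consistent.** Assume one agreement score per version. Endorsers (score 5) give consent 5 if the 2018 criteria are met and 1 otherwise. Among rejecters (score 1), a share q finds the version too strict and always gives 5; the rest find it too permissive and always give 1. With p the share of qualifying vignettes:
   - endorsers' mean = 1 + 4p
   - rejecters' mean = 1 + 4q
   - slope = [(1 + 4p) − (1 + 4q)] / (5 − 1) = p − q

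| q | Strict (p = 1/8) | Loose (p = 1/4) |
|---|---|---|
| 0 | +0.125 | +0.25 |
| 1/8 | 0 | +0.125 |
| 1/4 | −0.125 | 0 |
| 1/2 | −0.375 | −0.25 |
| 1 | −0.875 | −0.75 |

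   A simulation with strict coding (3,000 respondents, three ratings each) gave 0.124, 0.004, −0.114, −0.378 and −0.873 for the five values of q.

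4. **The same raters with criteria-met status in the model.** The slope among non-qualifying vignettes is [1 − (1 + 4q)]/4 = −q. Among qualifying vignettes it is [5 − (1 + 4q)]/4 = 1 − q. The interaction is their difference, 1.0 for every q (simulated 0.99 to 1.03).

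5. **Less extreme rejecters (strict coding).** Endorsers' gap between qualifying and non-qualifying vignettes is 4.
   - Rejecters who keep the rule but exclude mental illness accept 4 of 6 qualifying vignettes and no others: gap 4 × 4/6 = 2.67, interaction (4 − 2.67)/4 = 0.33.
   - Rejecters who drop only the no-option condition accept 6 of 6 qualifying and 6 of 42 others: gap 4 × (1 − 6/42) = 3.43, interaction (4 − 3.43)/4 = 0.14.

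   The size therefore still depends on why people reject. The sign stays positive: 4 is the largest gap the scale allows, so rejecters cannot exceed endorsers who apply the rule exactly.

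6. **Precision.** At the 3,000 expected records per group, qualifying ratings on strict coding number 3,000 × 3 × 1/8 = 1,125. With equal, independent errors, the interaction's standard error is 1/√[p(1 − p)] times that of the overall slope: 1/√(0.125 × 0.875) = 3.0 on strict coding and 1/√(0.25 × 0.75) = 2.3 on loose coding.

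7. **Newest version.** The Introduction's stated addition concerns substantiation of severity by diagnosis and prognosis. None of the permuted factors is that condition, so on this description the 2018 and newest versions receive the same coding for every vignette.

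**The case against.** The text does not say that criteria status will be left out. Secondary endpoints follow the primary model only so far as that is possible, the article is condensed, and a fuller plan could contain the interaction. This stands: the omission is inferred from the endpoint's wording and the one model family named. But the point is not about missing detail. The question, the endpoint and the model are all stated, and as stated they do not match.

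The slopes come from invented raters and assume one agreement score per version, whereas the article could also mean one score per criterion. The 2004 coding is inferred. All of this stands, so the figures show what can happen and do not predict what will.

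Each vignette also yields an open justification and a selection of decisive reasons, which could show directly which criteria a respondent used. They would be a useful supplement, but nothing ties them to endpoint 3, and the model named has consent as its outcome.

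A reader might infer that the endpoint cannot be estimated because many respondents see no qualifying vignette: (7/8)³ = 67% for the 2018 criteria and 75% for the terminal criterion on strict coding, 42% and 50% on loose coding. That does not follow. Versions are randomised, so the comparison can be made between respondents. For the same reason the simple slope is a valid average association; only its meaning is at issue. A reader might also infer that the authors would report consistent respondents as inconsistent. The article says nothing about how the sign would be interpreted.

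**Conclusion.** The concern holds as a mismatch between question and analysis target. Followed as written, endpoint 3 estimates an overall association whose sign, under strict coding and the raters assumed above, is that of 1/8 − q and so does not show whether people apply the guideline they endorse. That the sign can vary rests on two features in the documents: criteria that must hold jointly and components that are permuted. The particular values are illustrative, since no distribution of positions is given.

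Two stronger readings are not supported. First, the interaction does not give a measure of consistency free of the reasons for rejection; the examples of 0.33 and 0.14 show otherwise. Second, the vignettes' inability to separate the newest version from the 2018 one is no ground for removing the newest version from endpoint 3. The research question names it, and the endpoint does not promise to tell the two apart by vignette content. It is a limit on interpretation.

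The endpoint is secondary, the study is exploratory and no significance level is set. The change should be made, but it does not threaten the primary endpoint.

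**What to change.** - Code each of the 48 vignettes from its design factors as meeting or not meeting each guideline version, using the guideline texts shown to respondents. Add a sensitivity coding in which a present option may count as unacceptable.
- Make the agreement-by-criteria-met interaction on consent the main analysis of endpoint 3, allowing for three ratings per respondent. Read its sign as evidence of correspondence and its size with caution.
- Keep the newest version in endpoint 3, and state that on the Introduction's description no vignette factor separates it from the 2018 version, so a difference between those two results cannot be attributed to vignette content.
- Before coding, settle the newest version's date: 2021 in the Primary objective, case vignettes and Statistical analysis sections, 2022 in the Abstract, Introduction and Study design.

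The cost is a reworded endpoint and one derived variable per guideline version, plus the sensitivity coding. No new data or respondent burden is needed. The downside is a less precise estimate, by a factor of roughly 2 to 3 in standard error for the 2018 version under the simple assumptions above.

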### Importance of the research question

The regulation of PAD in psychiatric patients is subject to controversial discussions. It presents an extraordinarily challenging situation in medical practice and is of increasing relevance both for Switzerland and internationally, as evidenced by the rising incidence of PAD in mentally ill patients (see above). However, there is currently little scientific data on this issue (6).

With the present study, we want to contribute to the discussion regarding the need of regulating PAD in mentally ill patients. On the one hand, mentally ill patients with a wish to die must not experience any disadvantage compared to somatically ill patients, whilst at the same time, their vulnerability must be considered. On the other hand, treating physicians must be protected in their ethical integrity. Using an anonymous online survey, we aim to assess the attitude of the general population and medical professionals toward the current medico-ethical guidelines of the SAMS. Furthermore, we want to examine to what extent the public discussion corresponds to the current situation in clinical practice. The results of the study may also indicate to what extent stigmatization needs to be counteracted through public education or continuing medical education, should the survey show that prejudices against mentally ill patients are linked to the assessment of their wish to die.

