## Methods

### Study design

This is a monocentric prospective observational survey-based study. The study is exploratory and will consist of an online/telephone survey about PAD in somatic vs. mental illness in Switzerland on a sample of the general population from all three language regions (German, Italian, and French) as well as medical professionals working in the seven states (“cantons”) of Basel-Stadt, Basel-Landschaft, Aargau, Lucerne, Graubünden, Ticino, and Vaud. Each participant will be randomly assigned a somatic terminal, a somatic non-terminal, and a mental non-terminal case vignette. Furthermore, the attitude toward the ethical guidelines of the Swiss Medical Association of 2004, 2018, and 2022, as well as the stigmatization of mentally ill people will be assessed. The study questionnaire is described in detail below.

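### The stigma endpoint is worded more broadly than its objective, and the regression named for it cannot separate prejudice about mental illness from general opposition to PAD

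*Protocol article*

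**What the plan says.** All places are in the protocol article.

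- **Aim.** Under Primary objective, the stigma question concerns the mentally ill: "it examines to what extent the stigmatization of mentally ill persons is linked to the acceptance of their wish to die". Importance of the research question gives the intended use. The results may indicate a need for public or medical education should the survey show that "prejudices against mentally ill patients are linked to the assessment of their wish to die".
- **Research question and endpoint.** Research question 5 is broader: "Is there an association between the level of stigmatization and the assessment of whether a person should be granted access to PAD". Secondary endpoint 4, under Statistical analysis, follows that wording: "Association between the degree of stigmatization and the assessment of PAD". Neither names a vignette type.
- **Data.** Study design: "Each participant will be randomly assigned a somatic terminal, a somatic non-terminal, and a mental non-terminal case vignette". Each participant therefore gives two somatic ratings and one mental rating.
- **Analysis.** The primary endpoint gets a "simple regression analysis with the level of PAD consent as the dependent variable and type of illness as the independent variable", then a multiple regression on demographic factors. For the rest: "The secondary endpoints will be evaluated—as far as possible—with the same analyses". The only controls named are these: "The variables general population/medical professional and gender will be controlled for statistically whenever necessary". No stigma-by-illness-type term is mentioned.

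**The concern.** The study wants to learn whether people who stigmatize the mentally ill judge a mentally ill person's wish to die differently. A participant who scores high on stigma may also be more opposed to PAD for anyone. A single stigma slope adds the two tendencies together.

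What is at stake is the inference about education. A slope that only reflects general reluctance about PAD could be reported as prejudice against psychiatric patients. If somatic ratings are averaged in, a real prejudice confined to the mental case could also look much smaller than it is.

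**Working it through.** **Plan's own figures.** The protocol gives no effect size, SD or power for this endpoint. Its sample sizes (2,373 and 2,258) are margin-of-error figures and do not bear on the point. The usable inputs are three ratings per person, one of them mental (Study design), and 3,000 expected responses per group (Sample characteristics). Every slope, correlation, SD and intraclass correlation (ICC) below is an assumption.

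**Step 1: slopes under the possible readings.** Let b_M and b_S be the change in rating per SD of stigma in the mental and in each somatic vignette.

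- All three ratings: (2·b_S + b_M)/3
- Mental vignette only: b_M
- Contrast, mental minus somatic: b_M − b_S

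A simulation with 3,000 respondents and 300 repetitions agrees with the algebra. It took the mean of the two somatic slopes as comparator. The two were set equal, so the expected contrast is the same as against the somatic non-terminal vignette alone.

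| Assumed truth | b_M | b_S | All three | Mental only | Contrast |
|---|---|---|---|---|---|
| A: effect specific to mental case | -0.30 | 0 | -0.10 (simulated -0.099) | -0.30 (-0.299) | -0.30 (-0.299) |
| B: general opposition only | -0.30 | -0.30 | -0.30 (-0.300) | -0.30 (-0.300) | 0.00 (0.001) |
| C: both | -0.60 | -0.30 | -0.40 (-0.401) | -0.60 (-0.601) | -0.30 (-0.301) |

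In A, pooling leaves (2×0 − 0.30)/3 = -0.10. The factor of one third holds for any effect confined to the mental vignette. In B, the mental-only slope is as wrong as the pooled one, so restricting the analysis cures dilution but not confounding. Only the contrast recovers the specific effect in all three rows.

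**Step 2: size of the confounding.** If stigma has correlation r with general opposition, and opposition lowers every rating by L per SD, the spurious slope is −r·L under either reading:

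- r = 0.4, L = 0.6: -0.24
- both halved, r = 0.2, L = 0.3: -0.06

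**Step 3: limit of the contrast.** It cancels general opposition only if opposition moves both ratings equally. Suppose it moves the mental rating by -0.9 and the somatic non-terminal rating by -0.5, with r = 0.4. The contrast is then 0.4 × (−0.9 + 0.5) = -0.16 with no specific effect. The mental-only slope would be 0.4 × (−0.9) = -0.36. The bias is smaller but not gone.

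**Step 4: precision.** Take n = 3,000, rating SD 1.5 and within-person ICC ρ.

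- Variance of the mean of three ratings: 2.25·(ρ + (1−ρ)/3)
- Variance of the difference of two: 2·2.25·(1−ρ)

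At ρ = 0.4 these are 1.35 and 2.70. The slope SEs are √(1.35/3000) = 0.021 and √(2.70/3000) = 0.030, a ratio of 1.41. At ρ = 0.2 the variances are 1.05 and 3.60 (ratio 1.85). At ρ = 0.6 they are 1.65 and 1.80 (ratio 1.04). In scenario A at ρ = 0.4, estimate over SE is 0.30/0.030 = 10 for the contrast and 0.10/0.0212 = 4.7 for the pooled slope.

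**The case against.** The strongest reply has four parts.

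1. **Pooling is not in the text.** A reader might infer that endpoint 4 is defined as one association over all vignettes, and hence that dilution is built into the plan. Two things point that way. The questionnaire section headed as the assessment of PAD covers all three cases, and the primary regression must use somatic and mental ratings together. But no sentence says the stigma analysis pools them, and the objective and rationale point to the mental case. The dilution is therefore conditional on pooling.
2. **Some adjustment is planned.** The analyses include a multiple regression, and religious belief is among the demographics collected. A reader who infers that no confounder can be handled goes too far. Still, religion is not named as a covariate and stands for only part of a person's general attitude to PAD. The participant's own somatic ratings measure that attitude more directly.
3. **The study speaks of association, not cause, and research question 5 really is broad.** Both are correct. A mental-vignette slope answers the literal objective, and an overall slope answers research question 5. Neither can carry the inference about prejudice that the rationale draws.
4. **Model detail may sit in a full protocol or SAP not shown.** That may be so for the interaction term. The mismatch between objective, research question and endpoint is in the article itself.

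**Conclusion.** The point holds as a mismatch of wording and model. The objective and rationale concern the wish to die of mentally ill persons, while research question 5 and endpoint 4 concern PAD assessment in general. The regression named does not separate specific prejudice from general opposition on either reading.

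The confounding does not depend on pooling. Its size is −r·L, between -0.06 and -0.24 under the values assumed here. The shrinkage to one third depends on pooling and on an effect confined to the mental vignette. The documents supply none of the slopes, so these figures show the mechanism and do not predict a result.

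Severity is modest. The endpoint is secondary, the study is exploratory without significance levels, and the data to be collected already support the better analysis.

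**What to change.** - Reword endpoint 4 to match the objective, and say how research question 5 relates to it.
- Make the main estimate the stigma-by-case-type contrast, mental non-terminal against somatic non-terminal. The somatic non-terminal vignette is the cleaner comparator because the mental vignette is always non-terminal.
- Fit it to the within-person ratings with a participant random effect or errors clustered by participant. Equivalently, regress each person's rating difference (mental minus somatic non-terminal) on the stigma score.
- Report alongside it the mental-vignette slope and, for research question 5, the overall association.
- State that the contrast removes general PAD attitude only to the extent that it affects both ratings equally. Floor effects on the 5-point scale could also disturb this.

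The cost is one model term and a few sentences, with no new data. The contrast has a larger standard error than a main effect over all ratings: about 1.4 times at the assumed ICC of 0.4.
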